### Digital Interventions for health promotion

Recent developments and studies highlight the opportunities of digital interventions to address the described concerns for implementing and evaluating interventions in the health care sector and the current stage of change readiness. Interestingly, internet-based interventions have been rarely implemented in the healthcare sector so far [64]. Digital health promotion programs can come in different forms: Web-based trainings (WBT) are presented on a secured online platform and assessed through an internet browser either on a smartphone or on a computer/laptop [65, 66], whereas app-based interventions come with a smartphone application only [67, 68]. However, there are also hybrid forms such as web apps.

Digital Interventions can be a low-threshold opportunity for health promotion and are a promising possibility to achieve prevention goals [69, 70], even though eHealth literacy is sometimes missing [65]. The free allocation of time and flexibility of availability were evaluated on a positive note. Combining such apps with so-called “wearables”, such as smartwatches or fitness trackers, could allow us to continuously record health data and thus constitutes various opportunities in the context of prevention work (Gamification, Just-in-time-adaptive interventions). By implementing “wearables” into digital health applications (apps), health-related data (e.g., sleep patterns, eating patterns, and exercise) could be recorded and interventions that meet individual needs could be derived based on this data [66]. Previous studies already found positive effects of stress apps on wellbeing. Harrer et al. [67] for example found that app-based stress management interventions improved stress, anxiety, and depression in college students. Another example stems from research by Economides et al. [68] who found that a mindfulness app intervention reduced stress and irritability, while it also increased positive affect. A systematic review and meta-analysis on web- and computer-based interventions for stress reduction illustrates international research efforts. Included studies have been carried out in Western countries (Austria, Switzerland, Germany, Great Britain, the Netherlands, Norway, Sweden, and the USA) and Japan with studies predominantly having been conducted in the USA. The meta-analysis further underlines that digital interventions have shown positive effects on stress outcomes in different samples in the countries mentioned [71].

At the same time, expectations towards health apps are high, 70% of health app users believe that these can strengthen self-motivation and 56% think that app use can improve health education [72].

In order to establish long-term health behavior change, a high level of adherence motivation during the intervention implementation is necessary, and therefore individually tailored approaches may be beneficial. Often, the adherence for digital health promotion programs is rather low which reduces their effectiveness [73]. Individual tailoring [74] or gamification could be approaches to address this problem. In one meta-analysis, researchers found that web-based tailored interventions clearly outplayed generic interventions with respect to health behavior change [75]. In particular, non-tailored interventions were found to decrease user satisfaction [76].

However, the definition of a tailored health app is unclear due to the lack of a framework for individualized app elements. In one of the few reviews that adequately addresses this issue, the authors enumerate the Individualized Elements in the app and grade whether it is a tailored or non-tailored mHealth intervention [77]. The evidence of this review is clear, however, that there is a wide range of potential approaches for individualization and that these are often accompanied by established behavior change mechanisms, yet the effectiveness of individual elements must first be investigated in stand-alone interventions, as tailored mHealth interventions are often multicomponent in nature.

One approach to design individually tailored digital solutions could be a focus on users’ personalities. A smartphone app that focuses on stress reduction thus firstly needs to focus on personality characteristics as studies showed that personality characteristics are associated with specific coping behavior [78], app usage behavior, and receptivity to gamification elements [79]. Focusing on personality characteristics also allows for app-tailoring. Additionally, it needs to address users on their current state of readiness for behavioral change App modules that focus on conflict solving skills and communication techniques could work to address those issues. To the best of our knowledge, to date there are no studies investigating the effect of tailored mHealth interventions to reduce stress in the healthcare sector.

In summary, for the development of a digital health intervention, the specific combination of different contents has to be considered. These are (1) evidence-based feasible interventions, (2) tailoring and individualization, and (3) additional elements to gain adherence and long-term usage. Therefore, the present study aims to compare both web-based vs. app-based and tailored vs. non-tailored stress management interventions. All included types of interventions were previously found to improve users’ wellbeing in different facets. While generalized web-based interventions that are designed for a broad user population require less technical effort than those containing individualization, a lack of individual tailoring appears to be a central issue when it comes to user motivation and willingness for behavior change. Individual-tailored app-based interventions on the other hand could address this need but require high technical effort as they rely on complex structures. One-size-fits-all interventions that are accompanied by an individual telephone coaching may be another option to allow a certain level of individual tailoring. Therefore, it is of high importance to compare the different approaches with regard to cost-benefit considerations.

With fitcor, we provide healthcare and administrative workers specific digital interventions. This protocol describes a randomized controlled trial (RCT) in which we investigate the effectiveness of the fitcor interventions. Therefore, our aim is to identify the most beneficial digital intervention with respect to the following goals: (a) reduce stress and associated consequences and/or symptoms, (b) increase self-management and self-efficacy, and (c) increase adherence.

The proposed trial is needed to address these aims for four reasons. It includes samples from three different health care settings (1), namely hospitals, stationary elderly care homes, and ambulatory care, which allows to draw conclusions on similarities and differences between the effectiveness of the interventions in the specific settings. It allows comparison of different digital interventions with regard to topic, complexity, or biofeedback inclusion (2). Additionally, it enables investigating stress both from an objective perspective facilitating physiological measures as well as from a subjective perspective facilitating self-report measures (3). Finally, we can derive conclusions on long-term effects of the applied intervention through our longitudinal approach [4]. We expect that each intervention will benefit participants as they get free access to usually pricey digital health improvement programs. But at the same time, participants will have to invest some of their time to conduct all three measurement time points. Other than that, no harms are assumed to appear directly caused by the intervention. Next to the effects on different outcome parameters, the whole approach will give us more information about the required composition of individualization and modularization in different occupational groups.

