**Table 1 Tab1:**
[figure not shown]
Schedule of enrollment, interventions, and assessments: Recommendations for Interventional Trials (SPIRIT) chart of the enrollments and assessments during randomized controlled trials

The five intervention groups are as follows:Web-based digital stress management intervention (WBT only)Web-based and need-oriented digital stress management intervention (WBT + Need)Web-based and need-oriented digital stress management intervention with telephone coaching (WBT + Need + Coaching)App-based stress management interventions with sensory biofeedback (App + Biofeedback)App-based stress management intervention with sensory biofeedback and health report (App + Biofeedback + Report)

All participants of the intervention groups will receive a digital intervention. The waitlist control group will start the intervention after 8 weeks. Both, questionnaire and sensory data will be assessed:At baseline (*T*
_1_: pre-intervention/pre-waiting)At 8 weeks (*T*
_2_: post-intervention/post-waiting=pre-intervention)At 16 weeks (*T*
_3_: sustainability or post-intervention for waiting group; see Table 1).

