#### Intervention description

As described above, there are five different intervention scenarios, each including a WBT or an app, and each with different levels of individualization. This trial becomes particularly complex due to the need orientation of the WBT interventions. Depending on the needs of a person, he or she is assigned a different WBT. For example, a person who does not exercise enough and is very overweight is recommended a weight loss WBT, while a person who suffers from high stress levels is recommended a WBT with autogenic training or mindfulness. For this reason, a detailed list of the content covered in the respective apps or WBTs is provided in Table 2 below.

**Table 2 Tab2:** Detailed list of the contents of the various needs-specific app and WBT modifications

Focus	Sub-focus	App				WBT							
		AusGleich	BIG Balance	myCare+	GetRest	Nutrition	Weight loss	Physical Activity	Spine Gymnastics	Mindfulness	Hatha Yoga	Sleep and Stress	Autogenic training
Individualization	Direct biofeedback	x	x	x	x								
	AVEM patterns	x											
	Telephone coaching					x	x	x	x	x	x	x	x
	Vocational setting	x	x	x	x								
	Need orientation					x	x	x	x	x	x	x	x
Stress and relaxation	Problem-focused	x	x	x	x								
	Deep breathing	x	x	x	x					x	x	x	x
	Mindfulness	x	x	x	x					x	x	x	
	Goal setting	x	x	x	x		x	x		x		x	x
	Gratitude journal	x	x	x	x					x	x	x	
	Positive psychology	x	x	x	x					x	x	x	x
	Autogenic training	x	x	x	x					x	x	x	x
	Progressive muscle relaxation	x	x	x	x					x	x		
	Body perception	x	x	x	x					x	x		
	Stress physiology												x
Sleep	Sleep habits	x	x	x	x								
	Sleep and shift work	x	x	x	x								
	Healthy sleep	x	x	x	x							x	
Physical activity	Stretching and yoga	x	x	x	x			x			x		
	Fascia						x	x	x				
	Behavior change	X	x	x	x								
	Activity habits	x	x	x	x								
	Endurance training	x	x	x	x			x					
	Anatomy						x	x	x				
	Spine health								x				

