## Discussion

The development of a digital intervention to improve the individual’s abilities for stress management in different working settings, especially in the health sector, is facing several requirements. Next to the integration of evidence-based feasible interventions, these contents need to be tailored and individualized to gain adherence and long-term usage. Therefore, the main aim of the study is to compare web-based and app-based stress management interventions to identify the most beneficial digital intervention to (a) reduce stress and associated consequences and/or symptoms, (b) increase self-management and self-efficacy, and (c) increase adherence.

Regarding the overall aim, previous studies have shown that the nursing occupation is strongly linked to stress experiences [9]. The working conditions within the health care sector are accompanied by staff shortage and poor health outcomes, which were exacerbated by increased workloads during the pandemic [102]. Previous studies have shown chronic stress and resulting physical, cognitive, and emotional strains in nursing personnel [103, 104]. Regarding the physical conditions, chronic stress leads to reduced heart rate variability [21].

As administrative personnel do not have the same level of intimate encounters with patients, they are less likely to experience work stress. Also, shift work is an independent stressor, which is less of a problem for administrative personnel. Therefore, we suppose the two target groups within our study might show differences in their chronic stress conditions and referring physical reactions (expressed by heart rate). Moreover, it has been shown that the physical conditions might also lead to reduced sleep quality or duration [105]. With respect to the different nature of work-related burdens within nursing and administrative personnel, these circumstances might also lead to differences in individual sleep quality.

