One-size-fits-all interventions have been found to produce fewer desirable results than need-tailored interventions [63]. We expect biofeedback-based, need-tailored digital interventions to be superior in terms of stress reduction and physical activity improvements than generalized, nonspecific online courses. However, the presented biofeedback system has not been tested before systematically. It might therefore be the case that additional intervention necessities emerge by means of the sensor screenings. As an example, if sleep recovery is found to be of particular low quality, recommendations will be made to specifically target sleep in future interventions.

Next to the positive effects of tailoring the interventions to gain higher effects of individual stress responses, individualization might be expected to increase the adherence of the participants [112]. A continuous participation in an intervention program is necessary to gain positive adaption and long-term effects. The interventions of this study integrate different forms of strategies (e.g., tailoring, self-tracking) that are helpful to maintain a certain behavior [113, 114]. To our knowledge, there is no study that compared these different approaches within care settings, yet. Therefore, with this study, we detect new insights into the most beneficial composition of the program with respect to adherence according to the acceptance rates.

Further, moderators for intervention effects will be analyzed. For instance, a higher degree of usability for younger participants vs elderly participants may be apparent. However, it has recently been shown that elderly people are improving their e- and mHealth literacy [115]. Thus, whether or not relatively young participants profit more from the current intervention will be analyzed.

In summary, this trial integrated evidence-based contents demonstrating positive effects on stress management and converted these contents for the use of digital health in the context of healthcare work. Moreover, the approach integrates individualization to the digital offers to improve effectiveness and adherence.

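### App delivery and biofeedback always occur together and topic is not randomised, so the trial cannot support the stated comparisons by format, biofeedback inclusion or topic except as whole packages

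*Protocol article*

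**What the plan says.** The Introduction, under Digital Interventions for health promotion, sets out the purpose: "the present study aims to compare both web-based vs. app-based and tailored vs. non-tailored stress management interventions". A little further on, one of four reasons for the trial is: "It allows comparison of different digital interventions with regard to topic, complexity, or biofeedback inclusion". The Discussion repeats the platform comparison: "the main aim of the study is to compare web-based and app-based stress management interventions". It also states a hypothesis: "We expect biofeedback-based, need-tailored digital interventions to be superior in terms of stress reduction", with generic online courses as the comparator.

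The arms are listed under Study design, with Table 1. Three are web-based: WBT only, WBT + Need, and WBT + Need + Coaching. Two are app-based: App + Biofeedback, and App + Biofeedback + Report. There is also a waiting control group.

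Table 2, under Intervention description, marks direct biofeedback for all four apps and for none of the eight WBTs. On how a WBT is chosen, the same section says: "Depending on the needs of a person, he or she is assigned a different WBT". Its examples are a weight-loss course for someone inactive and very overweight, and autogenic training or mindfulness for someone highly stressed.

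**The concern.** A comparison by biofeedback inclusion needs at least two randomised arms that differ in biofeedback and share the delivery format. A comparison of web with app needs the reverse. The arm list has neither. A comparison by topic needs topic to be randomised, and here it is chosen from the participant's own needs.

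The interpretation of the results is at stake. The Introduction says that individually tailored apps take high technical effort, generic web courses take less, and the approaches should be weighed on cost and benefit. If the app arms did better, the article's wording would invite the conclusion that app delivery works, or that biofeedback works. The data would fit either, or neither if other app-only content were responsible. The Introduction itself notes that tailored digital programmes tend to have several components and that single elements need testing on their own. The Limitations section does not mention that this design cannot do so for format or biofeedback.

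**Working it through.** The article gives no figure to reproduce; the check is structural.

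**Inputs.** Arm labels from Study design; content marks from Table 2; the WBT assignment rule from Intervention description.

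**Step 1: code the arms** (1 = component present, following the arm labels).

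| Arm | App | Biofeedback | Need | Coaching | Report |
|---|---|---|---|---|---|
| 1 WBT only | 0 | 0 | 0 | 0 | 0 |
| 2 WBT + Need | 0 | 0 | 1 | 0 | 0 |
| 3 WBT + Need + Coaching | 0 | 0 | 1 | 1 | 0 |
| 4 App + Biofeedback | 1 | 1 | 0 | 0 | 0 |
| 5 App + Biofeedback + Report | 1 | 1 | 0 | 0 | 1 |

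The app and biofeedback columns are identical: (0, 0, 0, 1, 1).

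**Step 2: what can be estimated.** Assume additive effects a (app), b (biofeedback), n (need), c (coaching) and r (report). Then:

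- Arm 2 − Arm 1 = n
- Arm 3 − Arm 2 = c
- Arm 5 − Arm 4 = r
- Arm 4 − Arm 1 = a + b
- Arm 4 − Arm 2 = a + b − n

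No combination of arm means gives a or b alone; only a + b appears. With an intercept, the matrix has 6 columns and rank 5. Adding the waiting control group and an indicator for any intervention gives 7 columns and rank 6, and a and b remain inseparable. If the apps are instead coded as need-tailored (1 in the Need column for arms 4 and 5), the app and biofeedback columns are still identical, so the result does not depend on that choice.

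**Step 3: count the pairs.** Active-arm pairs: 5 × 4 / 2 = 10. Web-web 3, app-app 1, app-web 3 × 2 = 6. All six app-web pairs change format and biofeedback together. Pairs isolating format: 0 of 10. Pairs isolating biofeedback: 0 of 10.

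**Step 4: other content in the bundle.** Besides direct biofeedback, Table 2 marks six rows for all four apps and no WBT: vocational setting, problem-focused content, sleep habits, sleep and shift work, behaviour change, and activity habits. These move with the app as well, so a + b really stands for a wider bundle. Table 2 lists courses rather than arms, so it supports this reading but does not carry it; the overlap of app and biofeedback already follows from the arm list.

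**Step 5: topic.** Under the stated rule, people on a weight-loss course and people on a mindfulness course differ at baseline in activity, BMI and stress. The Primary outcomes section lists all three among the primary measures. A topic comparison is therefore confounded by need. This is weaker than the exact overlap in Step 2, because baseline adjustment can remove part of it, but randomisation gives no protection. The article does not say how topic is set in the WBT-only arm, so Arm 2 − Arm 1 may include a change of topic mix as well as need orientation.

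**Step 6: what would break the overlap.** As an illustration only, one further arm with an app but no biofeedback would raise the rank to 6 of 6 and make a and b separately estimable. Trial status gives March 2022 as the end of recruitment, so this is not a practical remedy.

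**The case against.** The best defence is that the trial asks about packages. Its main research question is which digital intervention is most efficient, and randomised arms answer that. Statistical analysis plans all interventions against the waiting group and comparisons between intervention groups, with no model of component effects. The sentence about biofeedback inclusion is rationale rather than a defined estimand, and the arms are explained as reflecting levels of individualisation. Cost-benefit between approaches is also properly a package question.

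Much of this stands. The package comparisons are sound, and nothing planned under Statistical analysis is invalidated. Complexity, which the same sentence names, can partly be compared through the steps within each platform, and tailored versus non-tailored can be compared within the web arms. What does not stand is the rationale itself: it claims comparison by topic and by biofeedback inclusion, and web versus app is described as an aim and later as the main aim. No analysis plan could give the design that property.

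A reader might go further and infer from the need-orientation row of Table 2 that no arm is both biofeedback-based and need-tailored, so that the Discussion's hypothesis has no arm to test it. The documents do not support that. The Introduction, Participant involvement, Secondary outcomes and Discussion all describe the apps as tailored or individualised, and the title of Table 2 covers both apps and WBTs. The hypothesis can be tested as app packages against the generic web course.

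A reader might also infer that the between-arm comparisons should be cut to a few contrasts to ease a multiplicity penalty. The article names neither ten tests nor a Bonferroni correction, and dropping cross-platform pairs would hinder the main research question.

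**Conclusion.** The concern holds as a limit on attribution. Format and biofeedback overlap exactly in the five active arms: six of six app-web pairs change both, and none of the ten pairs isolates either. Other app-only content belongs to the same bundle. Topic comparisons are non-randomised and confounded by baseline need, a lesser problem of the same kind. The statements in the Introduction and Discussion are therefore wrong as written for format, biofeedback inclusion and topic.

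The conclusion rests on reading the arm labels at face value, with Table 2 in agreement. The estimability result uses an additive coding; allowing interactions would add unknowns and could not separate the two effects. It does not depend on sample size or effect size. It does not mean that the trial fails its main question: a ranking of packages, and comparison with the waiting group, remain available.

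**What to change.** Change the wording in these places:

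- In the Introduction (aim and reasons for the trial) and where the Discussion restates the aim, limit the claims to comparisons of whole intervention packages.
- Present the Discussion's expectation about biofeedback as a package hypothesis: biofeedback app packages against generic web courses.
- State that an app-web difference will not be attributed to format or to biofeedback alone.
- Label any analysis by topic as non-randomised and exploratory.
- Name the randomised steps within a platform as the contrasts that support statements about added components: WBT + Need versus WBT only (need orientation, including any resulting change in topic); WBT + Need + Coaching versus WBT + Need (telephone coaching); App + Biofeedback + Report versus App + Biofeedback (health report).
- Keep the between-arm package comparisons that the main research question needs.

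No arm, sample size or data collection changes. The cost is that the trial gives up attributing effects to app delivery, biofeedback or topic, which the design could not support in any case.
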